## Abstract

**Background:**

Type 2 diabetes mellitus (T2DM) patients experience many psychosocial problems related to their diabetes. These often lead to emotional disorders such as distress, stress, anxiety and depression, resulting in decreased self-care, quality of life and disease control. The purpose of the current study is to evaluate the effectiveness of a brief value-based emotion-focused educational programme in adults with T2DM on diabetes-related distress (DRD), depressive symptoms, illness perceptions, quality of life, diabetes self-efficacy, self-care and clinical outcomes.

**Methods:**

A cluster randomised controlled trial will be conducted in 10 public health clinics in Malaysia, all providing diabetes care according to national clinical practice guidelines. Patients’ inclusion criteria: Malay, ≥ 18 years with T2DM for at least 2 years, on regular follow-up with one of three biomarkers HbA1c, systolic blood pressure and LDL-cholesterol sub-optimally controlled, and with a mean 17-item Diabetes Distress Scale (DDS-17) score ≥ 3. The intervention consists of four sessions and one booster over a period of 4 months that provide information and skills to assist patients in having proper perceptions of their T2DM including an understanding of the treatment targets, understanding and managing their emotions and goal-setting. The comparator is an attention-control group with three meetings over a similar period. With an estimated intra-cluster correlation coefficient ρ of 0.015, a cluster size of 20 and 20% non-completion, the trial will need to enroll 198 patients. Primary outcome: the between groups difference in proportion of patients achieving a mean DDS-17 score < 3 (non-significant distress) at 6 months post-intervention. Secondary outcomes will be the differences in the above mentioned variables between groups.

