### Participants

Patients will be screened using a structured case report form for eligibility. Eligible patients are Malay patients aged ≥ 18 years old with T2DM for at least 2 years. Their records must show that they are on regular follow-up with at least three visits in the past year and with blood results from the past 3 months. We will exclude patients who are enrolled in other clinical studies, pregnant or lactating, with known psychiatric/psychological disorders that could impair judgments and memory and patients who cannot read or understand English or Malay. Clinic staff involved in the screening will be instructed not to exclude any patients unless they fulfil one of the exclusion criteria, to avoid selection bias. In addition, participating patients must have current DRD with a mean 17-item Diabetes Distress Scale (DDS-17) score ≥ 3 and showing poor disease control, i.e. having one of these three biomarkers: HbA1c ≥ 8%, blood pressure ≥ 140/90 mmHg and LDL-C ≥ 2.6 mmol/L. Patients who scored ≥ 20 on the 9-item Patient Health Questionnaire (PHQ-9) which suggests a severe depression will be referred for further psychological attention and will not be invited to participate.

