### Outcomes

#### Primary outcome

Diabetes-related distress, measured with the 17-item Diabetes Distress Scale (DDS-17)

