### Sample size

In a previous study [23] the DDS-scores were normally distributed with a standard deviation of 0.8. If the true difference between the experimental and control means is 0.4 [23], we will need to study 64 experimental subjects and 64 control subjects with a power of 0.8 and a Type I error of 0.05. In a recent local study in 10 health clinics, the intraclass correlation coefficient (ICC) for HbA1c was 0.011 [70]. For cluster randomised clinical trials the standard sample size calculation needs to be inflated by a factor: 1 + (n – 1) ρ, where n is 20 (the average cluster size) and ρ is 0.015 (the estimated ICC for this study) [71]. This inflation factor is 1.285. This gives a total sample size of 165. Since we anticipate a 20% drop-out rate, we will ask eligible patients for participation until at least 198 have signed informed consent.

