### Statistical analyses

Data will be entered and checked for accuracy by two separate person before analysis. The principal investigator has the overall responsibility for compilation, maintenance and management of the study database. The database is stored on a password-protected computer in a locked office. Analyses will be carried out by both an intention-to-treat approach and a per protocol analysis. Data will be checked for normality and multicollinearity, and if necessary transformed. Estimates will be obtained with PASW 22.0 (SPSS, Chicago, IL).

One-way analysis of variance (ANOVA) and *χ*
^2^ tests, as appropriate, will be conducted to test for baseline differences across the two treatment conditions and to examine differences in outcomes between dropouts and continuing participants. The difference between the groups will be analysed using a 3-level mixed model to account for clustering of measurements within patients and patients within general practices. The random part of the model will include a random intercept per practice and an unstructured correlation matrix for the correlation of measurements within patients. The fixed part of the model will include the variables time (categorical), treatment group, a group*time interaction and the baseline DDS-17 score; the difference in DDS-17 score at 6-month will be tested using a linear contrast. If necessary a multiple imputation technique will be used for missing data. A calculated 95% confidence interval and two-sided α of 0.05 will be used to test significance.

We will evaluate how baseline predictors are related to baseline DDS-17 score (cross-sectional analyses). Second, we examine how the baseline predictors are related to linear change in DDS-17 score over time (prospective analyses). Third, we will explore a set of time-varying covariates: how changes in a predictor over time are related to changes in DDS-17 score over time. Similar statistical modelling will be carried out on secondary outcome measures. Continuous outcome variables will be analysed using linear mixed models and binary outcome variables using generalized linear mixed models.

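### The abstract makes the primary outcome a proportion, but the sample size and the specified DDS-17 test are for a mean score, so the stated 80% power does not belong to the declared outcome

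*Protocol article*

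**What the plan says.** Four places in the protocol article bear on this.

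- **Abstract, Methods.** The primary outcome is "the between groups difference in proportion of patients achieving a mean DDS-17 score < 3", assessed at 6 months. This is a yes/no outcome per patient. The same paragraph gives the enrolment of 198.
- **Outcomes, Primary outcome.** The entry reads "Diabetes-related distress, measured with the 17-item Diabetes Distress Scale (DDS-17", with no metric, cut-off or time point.
- **Sample size.** The premise is that "the DDS-scores were normally distributed with a standard deviation of 0.8", followed by "If the true difference between the experimental and control means is 0.4", "with a power of 0.8 and a Type I error of 0.05". The section gives no response proportion for either arm.
- **Statistical analyses.** The main model is a three-level mixed model adjusted for baseline DDS-17, in which "the difference in DDS-17 score at 6-month will be tested using a linear contrast". The section later says, after extending the modelling to secondary outcomes, that binary variables will be analysed with generalized linear mixed models. It does not mention the proportion below 3.

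**The concern.** A difference in proportions below a cut-off and a difference in mean scores are different estimands, and they can give different answers from the same data. A shift among patients who stay well above 3 moves the mean and leaves the proportion alone. Small changes around 3 do the reverse. As written, one reader would take the proportion as the result that decides the trial and another would take the mean, and each could cite the protocol.

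The second consequence concerns power. The abstract sets 198 beside the proportion as though that number had been calculated for it. Cutting a continuous score into two categories usually costs information, so the 80% cannot be assumed to carry over.

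**Working it through.** **Inputs from the document.** Mean difference 0.4, SD 0.8, power 0.80, type I error 0.05, average cluster size 20, ICC 0.015 and 20% drop-out (Sample size); two-sided test (Statistical analyses); success means mean DDS-17 below 3 (Abstract).

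**Inputs assumed.** The document gives no 6-month control mean and no response rate. I assume normal 6-month scores with SD 0.8 in both arms, a 0.4 shift, and the same design effect for the binary outcome. I let the control mean run from 2.0 to 4.4.

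**Step 1: reproduce the plan's figures.**

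- Standardised difference: 0.4 / 0.8 = 0.5. The normal approximation gives 63 per arm. The noncentral t gives 64 (power 0.8015), as stated.
- Design effect: 1 + (20 − 1) × 0.015 = 1.285.
- 128 × 1.285 = 164.5, so 165.
- 165 × 1.2 = 198.

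All three figures reproduce, and only a difference in means enters them.

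**Step 2: carry the same effect to the proportion.** The effective number per arm is 165 / 1.285 / 2 = 64.2. For control mean m:

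- control proportion below 3 = Φ((3 − m) / 0.8)
- intervention proportion below 3 = Φ((3 − (m − 0.4)) / 0.8)

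Power is for the two-sided two-proportion test (normal approximation, pooled variance under the null).

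| Control mean | Control below 3 | Intervention below 3 | Power |
|---|---|---|---|
| 2.0 | 0.894 | 0.960 | 0.30 |
| 2.4 | 0.773 | 0.894 | 0.45 |
| 2.8 | 0.599 | 0.773 | 0.57 |
| 3.0 | 0.500 | 0.691 | 0.60 |
| 3.2 | 0.401 | 0.599 | 0.61 |
| 3.4 | 0.309 | 0.500 | 0.60 |
| 3.6 | 0.227 | 0.401 | 0.57 |
| 4.0 | 0.106 | 0.227 | 0.45 |
| 4.4 | 0.040 | 0.106 | 0.30 |

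The best case written out, at m = 3.2: the difference is 0.599 − 0.401 = 0.197 before rounding. The null standard error is √(2 × 0.25 / 64.2) = 0.0883. The alternative standard error is √(2 × 0.401 × 0.599 / 64.2) = 0.0865. Power = Φ((0.197 − 1.96 × 0.0883) / 0.0865) = Φ(0.28) = 0.61. With unpooled variance and 64 per arm the maximum is about 0.63.

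**Step 3: vary the number analysed.** With 198 × 0.8 = 158.4 completers the maximum is 0.59. With all 198 and no drop-out it is 0.69.

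**Step 4: size needed for 80% in the best case.** 100 per arm before inflation. Then 2 × 100 × 1.285 = 257 completers. With the plan's own multiplication by 1.2 that is 309 enrolled (257 × 1.2 = 308.4). Dividing by 0.8 instead gives 322.

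Both power calculations leave out baseline adjustment and the small number of clusters (10).

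**The case against.** The strongest reply is that the body of the article is coherent by itself. The sample size and the main model both concern the mean score, so the abstract may simply describe the result in clinically readable terms. A fuller analysis plan may also settle the matter. This explains how the mismatch could arise, but it does not remove it. The abstract labels the proportion as primary, the Primary outcome section does not correct it, and a conflict between two statements in one document is not a detail left for elsewhere.

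Several stronger readings are tempting, and the documents do not support them.

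- **That the proportion has no analysis at all.** A method for binary outcomes is named. What is missing is its designation as the primary test of this proportion.
- **That the trial has 60% power as a matter of fact.** The document gives no control mean, response rate or SD for 6-month scores in patients selected at entry. The figure is a ceiling under the stated assumptions. A larger effect, roughly 24 to 25 percentage points near 50%, would restore 80%, but the plan states no such effect.
- **That the shared threshold invalidates the comparison.** Entry requires that "participating patients must have current DRD with a mean 17-item Diabetes Distress Scale (DDS-17) score ≥ 3", and success is a score below 3, so some patients will cross by measurement noise alone. That happens in both arms and does not by itself bias the contrast between them. The document gives no retest reliability from which to size it, and its questionnaire table gives a clinical reason for the cut-off.
- **That the sponsor means to choose between the two after seeing the data, or that the registration is wrong.** Nothing in the document shows intent, and the registry record is not at hand.

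**Conclusion.** The point holds as an inconsistency in the definition of the primary outcome: binary in the abstract, without a metric in the Primary outcome section, and continuous in the sample size and the specified DDS-17 test. This part needs no outside assumption. It also follows directly that the stated 80% power and the enrolment of 198 apply only to the mean difference.

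The size of the shortfall is conditional. It depends on normal 6-month scores, SD 0.8 in both arms, a 0.4 shift and an unchanged design effect of 1.285. On those terms, power with 165 analysed is about 30% to 61%, and no control mean brings it to 80%. The point should be settled before the data are analysed, because it decides which result is the trial's main one.

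**What to change.** State one primary outcome in the same words in the Abstract, Primary outcome, Sample size and Statistical analyses sections.

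The option that costs only wording is to make the baseline-adjusted difference in mean DDS-17 at the 6-month assessment primary, tested by the contrast already specified. The proportion with mean DDS-17 below 3 then becomes a named secondary outcome, analysed with the generalized linear mixed model already mentioned. The existing sample size and model fit this choice, and no extra data are needed. Check that the registration agrees, and align it if it does not.

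If the investigators prefer to keep the proportion as primary, they should name its model contrast as the primary test and restate the power from explicit response rates in each arm. On the plan's own effect size this would mean about 309 enrolled in the best case by the plan's drop-out arithmetic. The alternatives are a justified larger effect or an open statement of the lower power.

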**Discussion:**

We hypothesize that primary and secondary outcomes will improve significantly after the intervention compared to the comparator group. The results of this study can contribute to better care for T2DM patients with DRD.

**Trial registration:**

ClinicalTrials.gov NCT02730078. Registered on 29 March 2016, last updated on 4 January 2017.

**Electronic supplementary material:**

The online version of this article (doi:10.1186/s12902-017-0172-8) contains supplementary material, which is available to authorized users.

## Background

The prevalence of type 2 diabetes mellitus (T2DM) has increased during the past decades in many countries, with persistent high disease burden and healthcare cost [1]. In Malaysia, the prevalence of T2DM, diabetes-related complications and poor disease control and management are also increasing [2]. For many patients, it is difficult to cope with their chronic disease in daily life [3, 4]. As a result, many are experiencing complications (cardiovascular diseases, nephropathy, retinopathy and neuropathy) and psychological problems from uncontrolled diabetes [3, 5–7].

Studies in the United States (US) [8] and Germany [9] showed T2DM patients displaying one to twofold higher rates of affective disorders such as major depression, general anxiety, panic disorder and dysthymia compared to healthy adults, with the prevalence of depressive symptoms and distress 60–73% higher than the other affective and anxiety disorders [8]. We could demonstrate high rates of emotional burden experienced by patients with T2DM: about half of them had diabetes-related distress and about 30% had any degree of depression, with about 10% severe depression [10]. In an earlier study in 12 Malaysian public health clinics using the Depression, Anxiety and Stress Scale (DASS) questionnaire, the prevalence of depression, anxiety and stress symptoms among T2DM patients were 11.5, 30.5 and 12.5% respectively [11]. In a US survey the prevalence of untreated serious psychological distress was higher in T2DM patients compared to the total population and the non-diabetes population, and associated with young age, low education levels, low household income, obesity, current smoking, no leisure-time physical activity and presence of one or more micro- or macro-vascular complications [12]. Newly diagnosed T2DM patients who experience psychosocial problems often use negative coping strategies and expect more frequently that diabetes would negatively affect their future compared to patients who did not experience psychosocial problems [13]. Patients treated with insulin experienced higher diabetes distress compared to tablet- or diet-treated patients, and this emotional burden might cause insulin non-adherence if it is not improved [14, 15].

Diabetes-related distress (DRD) or diabetes distress is defined as the patient’s concerns about his/her disease management, (social) support, emotional burden, and access to care [16]. DRD and stress in a general sense were perceived similar in earlier literature until a more specific measure for DRD was developed [17]. Fisher et al. reported that what has been widely defined as “depression” among T2DM patients may be either a major depressive disorder or/and DRD, with only the latter displaying significant time-concordant relationships with glycaemic control (HbA1c) [18]. It is likely that DRD and depression are on the same scale of emotional disorders, but differ in severity, with other emotional disorders such as stress, dysthymia, anxiety in between [19]. Confusion between DRD and depression has recently been addressed and the authors had consented on emotional distress as the term to include both depression and DRD [20]. Since T2DM patients with DRD might not be capable of adequate self-care [21] it is recommended to take DRD into account in diabetes care even when it is considered mild [20].

Psychological interventions to improve both DRD and glycaemic control vary widely in their content and effectiveness [22, 23]. Interventions that addressed emotional aspects of coping with diabetes and took into account DRD showed promising results [24]. Recent systematic reviews show that psycho-education consisting of both emotion and cognition components are likely to be effective in reducing DRD [25, 26]. However, providing any psychological/emotional support by the healthcare team might pose a challenge to the existing healthcare system [20, 27]. Interventions with a highly specialised content require complex skills, involve physicians and/or psychologists and may require many sessions over a long period. Such interventions are hard to implement at the primary care level with its usually high patient-load, relatively low use of technologies, under-trained staff and budget constraints [28]. Effective psychological interventions in the primary care setting could be group-based [29], individualised to a person’s lifestyle, respecting an individual’s habits and routines; and can be conducted by health care providers [23, 26, 29–31] as well as non-expert mental health coaches [32].

### Conceptual framework

Optimal diabetes care requires emotionally healthy as well as cognitively competent patients [33, 34]. Emotion-focused and cognition-focused coping approaches have been shown to affect differentially on changes in lifestyle leading to psychological and physical benefits in adult T2DM patients [35]. Hence, both emotion and cognition are psychological aspects that should be taken in combination to achieve effective self-management [36]. It is hypothesized that emotional and cognitive domains that are in harmony with the personal value system and purpose in life may improve self-efficacy in patients with T2DM (Fig. 1) [37–41]. The Social Cognitive Theory of Self-regulation [42, 43] focuses attention on personal health beliefs and value systems as well as addresses emotional skills, with appropriate provision for the cognitive understanding of disease [44]. Patients’ negative beliefs about illness could influence physical and mental functioning [45, 46], and cause DRD and depression [47]. Furthermore, partners’ illness perception of T2DM could also affect self-management behaviours and psychological wellbeing of the patients [48–50]. Therefore, realistic illness perception in both the patients and their significant others will increase self-efficacy that would lead to better self-care and disease control.

**Fig. 1 Fig1:**
[figure not shown]
Conceptual framework

The emotional consequences of diabetes and its management are not limited to patients alone [51]. Social control attempts may have dual effects (appreciation and hostility) on recipients’ well-being, such that improved health behaviours may occur at the cost of increased emotional distress [52]. Therefore, spouses and family members can impede or facilitate the patient’s self-management [53, 54]. In this trial we will address the behaviours, feelings, and thoughts of both patients and their partners/significant others, and involving them throughout the programme’s activities for the patients. Since backsliding and regression to previous unhealthy lifestyles are not unusual for many T2DM patients, regular reinforcement by their significant family members of the uphold values, emotional skills and knowledge is necessary for the sustainability of the desired perceptions and behaviours [54, 55].

Accordingly, we developed an intervention that takes the patients’ beliefs into account besides addressing both the emotional and cognitional needs, involving their spouses or family members. The intervention will be delivered by nurses at the primary care level, targeting essential domains of health behaviours. It aims to provide information and skills to assist patients in adequate judgement and perceptions of their T2DM, including an understanding of the treatment targets, understanding and managing their emotions and goal-setting [56]. The intervention is culturally appropriate and competent through its targeted participants of single ethnicity and delivered by healthcare providers of the same ethnicity who will be trained to deliver the intervention in a compassionate and sensitive manner, taking into account the patients’ cultural beliefs, behaviours and needs [57].

### Aims of the trial

This study aims to assess the effectiveness and appreciation of a value-based emotion-cognition-focused educational programme in Malay adults with T2DM (VEMOFIT) delivered by Malay health clinic nurses. As the nurses are the deliverers of the intervention, the health clinics are the unit of randomisation. A cluster randomisation can prevent contamination through social and professional interactions between patients-patients and patients-nurses, respectively, and by preference of patient or physician.

It is hypothesized that the VEMOFIT will be appreciated by the participating patients and will be significant in reducing DRD, depressive symptoms, improving illness perception, health related quality of life, self-efficacy, health behaviour change (self-management), disease control (HbA1c, blood pressure, lipids) and healthcare utilization compared to before the intervention, and compared to attention meetings plus usual care. The rationale for using an attention control group (instead of a ‘usual care’ control group) is to distinguish the effectiveness of an intervention from personal attention provided by the healthcare team. Participants in both groups receive personal attention, but only the intervention group receives the VEMOFIT. The control group in this study gets significantly more attention with regards to their healthcare experience compared to usual diabetes care.

